Microbiological facilities are not available at most frontline healthcare settings. Most research on antimicrobial resistance (AMR) in China has, therefore, drawn on patient data collected in urban teaching hospitals. Because patients can choose to attend facilities at any level of the three-tier health system (community clinics, township health centres or county-level hospitals) and care pathways do not follow a predictable pattern of upwards referral, the extent to which antibiotic prescribing in urban hospitals drives the spread of antibiotic resistance in the wider population is currently unknown. The often asserted high burden of AMR in China may be misleading since current assumptions are based on potential pathogens isolated in selected microbiology laboratories enrolled in the national surveillance system and it is uncertain if this reflects the incidence of resistance in non-hospitalised patients with mild to moderate infection receiving antibiotics, most of whom do not have samples sent to the laboratory.^23 24^ UK data indicates that 1:35 patients presenting to their General Practitioners (GPs) with acute cough have microbiological sampling and perhaps 1:5 with urinary tract infection (UTI).^25^ This data indicates that resistance rates to key antibiotics based on biased laboratory data may be over-emphasised.^26 27^

There is a need for comprehensive and systematic assessment of prescribing and purchasing practices in the context of China’s unique health systems and policies, to identify potential targets for interventions to optimise prescribing and consumption. There are also crucial gaps in evidence regarding antibiotic resistance and its determinants in rural communities and health facilities at village and township levels in China and it is important to investigate the possibility of introducing routine monitoring of prevalence and epidemiology of AMR in these settings.

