### Participants

The microbiological substudy aims to recruit a total of 1550 patients (1000 with exacerbation of chronic obstructive pulmonary disease (COPD) and 555 with UTI). We estimate that this will yield 200 *Escherichia coli* isolates and 100 *Streptococcus pneumoniae* isolates, which should provide sufficient power to allow us to estimate key antibiotic susceptibilities (objective 4), on the assumption that:

40% of UTI samples will yield a pathogen.25% of COPD samples will yield a pathogen.90% of pathogens isolated from urine will be *E. coli.*40% of pathogens isolated from sputum will be *S. pneumoniae.*In *E. coli*, resistance to nitrofurantoin, fosfomycin and co-amoxiclav will be <5% and resistance to cephalosporins and fluoroquinolones 50%–60%.^28^In *S. pneumoniae*, penicillin resistance will be 12.5% and erythromycin resistance 90%.^29^

Inclusion criteria of patients are male or female who are: (1) 18 years or older and able to give consent to participate in the microbiological study, exit survey and/or follow-up interviews; (2) presenting to the recruitment site for his/her current illness for the first time during the study period and (3) diagnosed by the attending doctor as having one or more of the following: UTI, exacerbation of COPD, upper respiratory tract infection (RTI) with productive cough and sore throat. These patients will be selected via ‘consecutive sampling’ in which, when a start date has been determined, the recruitment continues daily (7 days a week) thereafter, between 08:00 and 17:00 hours or 09:00 and 18:00 hours on alternate days, until the target numbers have been reached. All incoming patients to the site village clinics and township health centres who meet the inclusion criteria during any study day are invited to participate. This is a pragmatic approach to sampling since patient record systems do not allow the flexibility to carry out random sampling, and ongoing recruitment will ensure the most efficient use of staff and resources in this setting.

Qualitative study participants will include: (1) patients visiting the selected village clinics and township health centres during the study period; (2) customers visiting the selected retail pharmacies during the study period; (3) doctors within the clinics or health centres for treatment of RTIs/UTIs; (4) salespersons working within the selected retail pharmacies.

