On arrival of any batch of specimens at AMU central lab, a designated technician will perform standard specimen assessment and pretreatment and then bacteria inoculation, identification and susceptibility tests. Sputum and throat swab specimens will be inoculated on four plates (a blood agar plate, a MacConkey agar plate, a chocolate agar plate and a chrome agar plate); and urine specimens inoculated on two plates (a blood agar plate and a MacConkey agar plate). The inoculated blood agar and chocolate agar plates will be cultured and incubated in an atmosphere of 5% CO_2_ at 35°C; the MacConkey agar and the chrome agar plates, incubated in air at 35°C. The incubation time will be 18–24 hours plus an additional 24 hours if no bacteria are observed for the first period. Bacteria identification will use automated methods, that is, the MicroscanWalkaway-96 System with PC33 (for gram-positive bacteria) or NC50 (for gram-negative bacteria) kits and also according to different biochemical reactions as follows: (1) *E. coli* chrome agar/VITEK2 or MALDI-TOF; (2) *S. pneumoniae* optochin/biochemistry; (3) *Haemophilus influenzae* X+V factors or MALDI-TOF and (4) *Moraxella catarrhalis* MALDI-TOF. For the bacteria susceptibilities, automated methods will be used (VITEK2 and MicroScan Walk Away 96 plus) along with disk diffusion and agar dilution methods (according to CLSI). Multidrug resistance will be defined according to standard criteria as set out by Magiorakos *et al*.^30^Antimicrobial susceptibility data on the key pathogens identified in community sampling will be extracted from the existing diagnostic laboratory databases for comparison with isolates from village clinics and county hospitals. A timeline for data collection can be found in online supplementary appendix table 1; a full list of bacterial isolates and susceptibility testing can be found in online supplementary appendix table 2.

10.1136/bmjopen-2018-027819.supp1Supplementary data

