### Data analysis

#### Quantitative analysis (objectives 1–4)

Data from the microbiological testing, review of clinical records and exit surveys will be analysed quantitatively to investigate prevalence of infection and rates of resistance, relationships between infection/resistance rates and patient characteristics and feasibility of routine microbiological testing in rural clinics. The feasibility of obtaining community-based samples of common pathogens and determining their antibiotic sensitivities (objective 1) will be examined by: (1) ratios of patients who have provided specimens versus those who have refused and their reasons for doing so; (2) percentages of specimens assessed as being properly collected, preserved and shipped by designated microbiological technicians; (3) ratios of positive versus negative attitudes toward giving specimens among the exit interviewees and views of the participating doctors. Prevalence of pathogens and AMR (objective 2) will be assessed by: (1) estimating percentages of pathogen positive specimens in terms of all and specific bacteria by diagnosis, type of specimen, patient-reported symptoms, previous treatment history and sociodemographics; (2) calculating percentages of resistant pathogens by type of bacteria and antibiotics and (3) comparing, using χ² test, these pathogen and resistance rates in non-hospitalised patients with those from analyses of data from large urban hospitals. We will produce a descriptive analysis of patient record systems and electronic record completeness and accuracy (objective 3). If sample sizes allow it, descriptive analyses may be followed by analytical studies to explore relationships between pathogen types and susceptibilities and patient characteristics such as presenting symptoms, clinical diagnosis, prior use of antibiotics and demographics (objective 4).

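### The objective 2 chi-square sets adult first-visit outpatients against hospital laboratory data with no stated age, specimen, period or one-isolate-per-patient rule, and its positivity comparison lacks a like denominator

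*Protocol article*

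**What the plan says.** Objective 2 (Box 1) carries the study's one explicit hypothesis: resistance is less common in non-hospitalised patients than in samples from large urban hospitals, which hold a larger share of inpatients.

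The section Quantitative analysis (objectives 1–4) first estimates pathogen positivity by diagnosis, specimen type and patient features. It then moves to "calculating percentages of resistant pathogens by type of bacteria and antibiotics". The third step is the test itself: "comparing, using χ² test", applied to "these pathogen and resistance rates in non-hospitalised patients with those from analyses of data from large urban hospitals". No adjustment is named for it. Analyses by patient characteristics appear later, depend on sample size, and are assigned to objective 4.

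The community sample is described under Participants and Specimen collection. Patients are "18 years or older and able to give consent", at first presentation of the current illness, with UTI, COPD exacerbation or upper respiratory infection, giving sputum, throat swab or urine.

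The hospital side is described in one sentence under Specimen collection and microbiological testing: "Antimicrobial susceptibility data on the key pathogens identified in community sampling will be extracted from the existing diagnostic laboratory databases". The purpose that this sentence gives for the extraction is worded "for comparison with isolates from village clinics and county hospitals".

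**The concern.** The test is fixed in the text, and it takes the two sides as they come. If the hospital extract differs from the community sample in age range, in the specimens that yielded the isolates, or in how often one patient is counted, those differences pass straight into the chi-square. None of them is what objective 2 asks about. They could produce a difference when like patients have the same resistance, or hide one that exists.

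The test also covers pathogen positivity. That rate depends on who is cultured, and the two sides choose whom to culture in different ways. The Introduction makes this point itself when it says of non-hospitalised patients with mild to moderate infection: "most of whom do not have samples sent to the laboratory".

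At stake is the reading of the only stated test of the study's explicit hypothesis.

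**Working it through.** **The plan's own figure.** Inputs are from Participants. E. coli: 555 × 0.40 × 0.90 = 199.8, stated as 200. S. pneumoniae: 1000 × 0.25 × 0.40 = 100, stated as 100. Both reproduce. They are justified for estimating susceptibilities (labelled objective 4). For the objective 2 test the article gives no significance level, sidedness, target difference or number of hospital isolates.

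**The two sides as described.**

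| Feature | Community sample | Hospital extract |
|---|---|---|
| Age | 18 or older | none stated |
| Specimen | sputum, throat swab, urine | none stated |
| Repeat isolates | largely excluded by the first-presentation rule | none stated |
| Period | study period | none stated |
| Species and drug | by species and antibiotic | key pathogens only |
| Care setting | non-hospitalised | mixed; part of the hypothesis |

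**What an artefactual gap would do.** Assumptions: two-sided 5% level; 200 community E. coli isolates at 50% resistance (the low end of the plan's 50%–60% for cephalosporins and fluoroquinolones); crude hospital rate 60%; hospital count n2 = 200, 1000 or 5000. Two ways to reach 60% when like patients are at 50% on both sides:

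- Case mix: half the hospital isolates come from strata 20 points more resistant. 0.5 × 20 = 10 points.
- Repeat isolates: resistant patients contribute 1.5 isolates each, susceptible patients 1.0. (0.5 × 1.5) / (0.5 × 1.5 + 0.5 × 1.0) = 0.75 / 1.25 = 0.60.

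Probability of a significant result = Φ[(|p1 − p2| − 1.96 × SE0) / SE1], where SE0 = √[p(1 − p)(1/n1 + 1/n2)] with p the pooled proportion, and SE1 = √[p1(1 − p1)/n1 + p2(1 − p2)/n2].

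- n2 = 200: p = 0.550, SE0 = 0.0498, SE1 = 0.0495; Φ(0.05) = 0.52
- n2 = 1000: p = 0.583, SE0 = 0.0382, SE1 = 0.0386; Φ(0.65) = 0.74
- n2 = 5000: p = 0.596, SE0 = 0.0354, SE1 = 0.0360; Φ(0.85) = 0.80

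**Masking.** These are also the powers for a true gap of 50% against 60%. If half the hospital isolates come from strata 10 points less resistant, the crude hospital rate is 60 − 0.5 × 10 = 55%, and the same formula gives 0.17, 0.25 and 0.29. If those strata are 20 points lower, the crude gap is zero.

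**Sensitivity.** With 25% to 75% of hospital isolates from other strata, 10 to 30 points more resistant, the crude gap runs from 0.25 × 10 = 2.5 to 0.75 × 30 = 22.5 points, and the probability from 0.07 to about 1.0. Nothing in the document narrows this range.

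**Repeats unrelated to resistance.** With m fully correlated isolates per hospital patient, the true variance is proportional to 1/200 + m/n2, against the nominal 1/200 + 1/n2. The effective critical value is 1.96 × √(nominal/true). For m = 2 the type I error is 0.11, 0.07 and 0.054 at n2 = 200, 1000 and 5000. With a large extract this is negligible; repeats matter chiefly when they go with resistance.

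**Positivity.** In the study the rate is positives over specimens obtained when every eligible patient is invited. In routine care a clinician decides whether to send a specimen; the Introduction cites UK figures of 1:35 for acute cough and perhaps 1:5 for UTI. The extract as described holds susceptibility results on identified pathogens, so it counts positive cultures and gives no number of specimens cultured.

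**The case against.** Four points can be made for the plan.

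- **Silence in a condensed article.** Age limits, specimen filters and de-duplication may sit in the full protocol. This stands against the tempting reading that the hospital database is unrestricted. The article never says so, nor that the extract holds children, blood or wound isolates, or repeats. One can say only that no such restriction is stated. It does not remove the chi-square or the positivity comparison, which are stated.
- **Part of the contrast is the hypothesis.** The comparator is the hospital laboratory figure, whose inpatient share Box 1 names and whose selective sampling the Introduction questions. This stands: neither should be treated simply as confounding. A reader might also infer that a significant result would be credited causally to setting, but the article makes no such claim. Age range, specimen type and repeat isolates are not in the hypothesis.
- **The rates are already stratified.** Species and drug are handled for resistance. Specimen type is named for positivity and could be carried into the test. For resistance, neither specimen nor age is named.
- **The probabilities are ordinary test power at chosen gaps.** This stands. They show what follows if an artefact of that size exists, not that one does.

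**Conclusion.** The point holds in limited form. The plan fixes an unadjusted chi-square between a tightly defined adult outpatient sample and hospital data whose only stated limit is key pathogens. Age, specimen type and repeat isolates can therefore create or hide a difference in resistance. The size and direction cannot be derived from the document; the 0.52 to 0.80 figures rest on an assumed 10-point artefact, an assumed two-sided 5% level and assumed hospital counts.

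The positivity test is the firmer part. Its denominators differ in kind, and the described extract does not supply one for the hospital side. That follows from the text without any assumed figure.

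The comparator also needs reconciling. Box 1 and the analysis section name large urban hospitals. The extraction sentence names village clinics and county hospitals, and can be read as placing county hospitals on either side of the comparison.

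This should be corrected before the hospital data are analysed, but it ranks below a must-fix: the study is largely about feasibility, and the comparison is part of one of seven objectives. Confidence is moderate, because a fuller document may already contain extraction rules.

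**What to change.** 1. Restrict the hospital extract to adults, to urine or respiratory specimens matching the community specimens, to the same calendar period, and to the first isolate per patient per species.
2. Compare resistance only, within species and specimen type, by Mantel-Haenszel or by logistic regression adjusted for age group and sex. Show hospital inpatients and outpatients separately; do not adjust the inpatient share away.
3. Drop the chi-square on pathogen positivity. Report community positivity as an estimate.
4. If only aggregate hospital tables can be had, label the comparison descriptive.
5. Name the comparator hospitals once and use the same name in Box 1, the extraction sentence and the analysis section.

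The cost is a tighter data request, a slightly longer analysis, fewer hospital isolates and somewhat wider intervals. The loss is modest while the 200 community isolates dominate the variance. With 50% on both sides, the 95% half-width for the difference is 1.96 × √(0.25/200 + 0.25/n2): 7.1 points at n2 = 5000, 7.6 at 1000 and 9.8 at 200.

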#### Qualitative analysis (objectives 5–7)

Analysis of the qualitative data (in-depth interviews, observations) will focus on identifying characteristic patterns in treatment-seeking pathways to antibiotic use among patients and antibiotic purchasers (objective 5) and on identifying key social, cultural, health systems and behavioural determinants of both antibiotic prescribing and provision among healthcare providers and of antibiotic use among residents (objective 6). Thematic and framework analysis will be undertaken for each of the four qualitative datasets using a similar approach. Following translation of a subset of interviews from each data set, members of the research team will independently free code a minimum of three interview transcripts in Mandarin or English and then meet to compare and finalise a code list. Further interviews will be coded thematically in batches in the software package NVivo 12 using the agreed codes until all data have been coded. Each interviewer will also summarise each interview transcript by entering a summary of the coded data in a Framework using Excel. Pile sorts will be analysed using Johnson's Hierarchical Cluster analysis, providing a two-dimensional concept mapping of the terms that are most frequently grouped together.

The occurrence of resulting themes will also be used to produce theme frequency maps and theme networks via NVivo or UCINET for different groups of participants and different topics.

Analysis of antibiotics-related pathways comprises identifying both a complete set of paths for common RTIs/UTIs and factors affecting patient trajectories among these pathways. Anticipated path sets to be produced include a general path set applicable for both RTIs and UTIs and an RTI and UTI-specific path set, respectively. Similarly, factor sets of interest in this study comprise combinations of factors that affect selection between: (1) doing nothing versus taking action; (2) self-care versus professional treatment; (3) western medicine versus traditional Chinese medicine; (4) antibiotics versus non-antibiotics therapy.

#### Analytic synthesis

Development of interventions for optimising antibiotics use (objective 7) will build on findings from both quantitative and qualitative analyses. It will also analyse the pathways and determinants identified from this study in relation to the Behaviour Change Wheel, a theoretical framework developed from 19 frameworks of behaviour change identified in a systematic literature review.^33^ The COM-B (‘capability’, ‘opportunity’, ‘motivation’ and ‘behaviour’) model, which recognises behaviour as part of an interacting system, will be used to identify key modifiable influences leading to the use of antibiotics and subsequently, inform recommendations for interventions to optimise antibiotic use.

### Patient and public involvement

Development of the research question was informed by patients’ experiences and preferences as documented in a previous study.^19^ The results will be disseminated to study participants and other stakeholders through a local dissemination workshop to be held at the end of this study and through short summaries of research findings.

## Ethics and dissemination

This protocol is rooted in a multidisciplinary collaboration between institutions in the UK and China. Investigators will benefit from exchange of academic knowledge and methodologies and will gain situational awareness which extends beyond their own area of expertise. This will lead to greater depth of insight into the scope and interrelatedness of influencing factors and allow the team to analyse and interpret study results with full awareness of the complexity of drivers of AMR and antibiotic use in rural Anhui province. The research will provide academics with a documented case study of how to conduct large scale research involving a multidisciplinary team across two countries, as well as a ‘worked example’ of research capacity-building through academic collaboration for the benefit of a middle-income country. Regular workshops will allow the China and UK research teams to exchange ideas and insights throughout the duration of the study. Lessons from this study will be shared with the wider academic community through peer-reviewed publications and conference presentations.

This innovative study will provide the first systematic documentation of routes and means to antibiotic use by residents at lower ends of the healthcare system (township and village clinics) in China and assess the feasibility of routine microbiological testing and analysis of antimicrobial sensitivities in the context of information from clinic healthcare records.

Findings from the study will be summarised for the benefit of public health policymakers, health professionals and health service managers in China and elsewhere. A final workshop will be held for the purpose of presenting the evidence generated by this study and working with local and regional stakeholders to translate this evidence into public health action.
